### Ethical approval

The study has received full ethics approval from the New Zealand Health and Disability Ethics Committee (HDEC, reference 18/CEN/48), and has been subject to Māori consultation^1^ with the Ngāi Tahu Research Committee (10 April 2018).

### Participants

Participants will be recruited from the forensic and rehabilitation mental health service from May 2018 until November 2020 (approximately). Participants will be recruited from inpatient, custodial, and community settings and must all be current patients of the forensic and rehabilitation service.

The eligibility criteria are as follows:
Age between 18 and 65 yearsA lifetime history of a psychotic disorder or a mood disorder with psychotic features diagnosed according to ICD-10 or DSM-5 criteriaMeeting diagnostic criteria for PTSD (Clinician Administered PTSD Scale (CAPS))Current patient of the forensic and rehabilitation mental health servicesCompetent to provide informed consentLikely to remain in the area for the 6-month trial duration (i.e., if a prisoner, release date at least 6 months away; if a patient within a forensic mental health service, their anticipated discharge is at least 6 months away)

To ensure “real world” generalizability of study results, we are keeping exclusion criteria to a minimum. The exclusion criteria are as follows:
High suicidality, operationalized as the combination of having a high suicidality score on the Mini International Neuropsychiatric Interview (MINI-plus) or with a suicide attempt within the past 6 monthsMental state considered by the treating psychiatrist as too unstable to participate in the trial (participants may be experiencing chronic low-grade symptoms, but cannot be acutely psychotic)Insufficient competence in the English language

The only intervention that is not permitted during the trial is the administration of EMDR by an external treatment provider. If participants intend to access EMDR through a private provider or Accident Compensation Corporation services (New Zealand’s no-fault accidental injury scheme) during the trial period, they will be ineligible for inclusion. Other interventions (e.g., psychological therapy, medication) are permitted.

### Recruitment

As part of the standard forensic care contacts, people who clinicians consider may fulfill the study criteria (i.e., have a serious mental illness, possible PTSD, and are competent to consent) will be given an information sheet about the project and invited to complete the Trauma Screening Questionnaire (TSQ) [26] by their clinician. The TSQ is a screening test for PTSD which has demonstrated adequate sensitivity and specificity, and good criterion validity [27]. If participants have a TSQ score ≥ 6 (or ≥ 5 for the subset of participants taking therapeutic doses of marked or moderately sedating antipsychotics, specifically clozapine ≥ 250 mg/day, olanzapine ≥ 15 mg/day, or quetiapine ≥ 300 mg/day [28], as this group experiences excessive sleep [29] and for whom we will exclude the disrupted sleep question) they will be eligible for formal PTSD assessment. Potential participants who verbally consent to receive more information about the study will be contacted by one of the investigators (either by telephone or if they do not have a telephone, for example if they are in custodial care, then through their clinical team) to arrange a face-to-face meeting. Patients can also be referred directly by their treating teams for an inclusion interview if they have a clinical diagnosis of PTSD.

At the face-to-face meeting, more detailed verbal information about the study will be provided by one of the investigators and the potential participant will have the opportunity to ask further questions about the study. Screening for suicidality will also take place at this stage (as previously described). People at high risk for suicidality will be excluded.

If the person decides to participate, the investigator will obtain written informed consent after explaining the purpose and content of the study, rights of participants, and confidentiality. An appointment will be made for confirmation of a PTSD diagnosis.

At the inclusion assessment, the researchers will administer the Clinician Administered PTSD Scale (CAPS) [30] structured interview to determine both eligibility for the trial and also the severity of symptoms at baseline. A positive CAPS is considered the gold standard in determining the presence of diagnoses of PTSD [31], with strong retest and inter-rater reliability, internal consistency, convergent and discriminant validity, diagnostic utility, and sensitivity to change [32].

Eligible patients will provide informed consent and complete the baseline assessments.

The outcome measures are assessed at baseline (T0), again following treatment at 2 months (T1), and then 6 months (26 weeks) after treatment started (T2). The outcome measures are described in detail in the following pages.

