**Methods:**

This is a single-blind, randomized controlled trial comparing EMDR therapy to the waiting list (routine care). Adult forensic mental health service users (*n* = 46) with SMI and meeting the criteria for PTSD will be included in the study. Participants will be randomized after baseline assessment to either treatment as usual plus waiting list for EMDR or to treatment as usual plus EMDR. The EMDR condition comprises nine sessions, around 60 min in length delivered weekly, the first of which is a case conceptualization session. The primary outcomes are clinician and participant-rated symptoms of PTSD, and adverse events. Secondary outcomes include psychotic symptoms, social functioning, level of disability, self-esteem, depressive symptoms, post-trauma cognitions, and broad domains of complex posttraumatic difficulties. A trained assessor blinded to the treatment condition will assess outcomes at baseline, 10 weeks, and 6 months. Additionally, grounded theory qualitative methods will be used to explore participant experience of EMDR for a subset of participants.

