### Randomization, allocation concealment, and blinding

Consenting participants will receive the pre-treatment (T0) measurements. After T0, participants will be randomly assigned to either the EMDR or treatment as usual group. An independent research manager at the District Health Board research office (who is not involved in the study) will generate the random sequence. This allocation sequence will be computer-generated and non-stratified with varying block sizes, which will not be disclosed to the researchers to ensure concealment. After randomization, the research office will notify the trial coordinator from the research team as to the allocation. To ensure allocation concealment, the randomization code will not be released until after the participant has been recruited into the trial, which takes place after all baseline measurements have been completed.

After allocation, the participants will be informed which group they are in. Hence, neither the participants nor the specialized therapists who deliver EMDR will be blinded to the allocation (as it is not practical to undertake blinded EMDR). However, outcome assessors will be blinded to treatment allocation, as will those performing data entry and the trial statistician (MW). Assessors and therapists will emphasize the importance of blinding to the participants and remind them not to reveal the randomized treatment condition. Assessors will avoid contact with the therapists and other caregivers. Assessors will be asked to report any case of unblinding, in which case, another assessor will repeat the entire measurement.

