#### Outcome measures

A range of primary, secondary, and tertiary outcome measures (all outlined in the following, see Fig. 2) will be administered at baseline (T0), post treatment (T1, at 10 weeks), and at 6-month follow-up (T2). After T2, participants will be invited to engage in a semi-structured interview (see Subjective experiences of EMDR: qualitative data collection) to gather data on their subjective experience of PTSD and EMDR.

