**Fig. 2 Fig2:**
[figure not shown]
Standard Protocol Items: Recommendations for Interventional Trials (SPIRIT) figure. AEQ, Adverse Events Questionnaire; BDI-II, Beck Depression Inventory—second edition; CAPS, Clinician Administered PTSD Scale; EMDR, eye movement desensitization and reprocessing; PSS-SR, Posttraumatic Stress Disorder Symptom Scale—Self-Report; PTCI, Posttraumatic Cognitions Inventory; PSYRATS, Psychotic Symptom Rating Scales; RSES, Rosenberg Self-Esteem Scale; SFS, Social Functioning Scale; TAAS, Treatment Acceptability/Adherence Scale; TSI-2, Trauma Symptom Inventory—second edition; WHODAS, World Health Organization Disability Assessment Scale

T2 is the starting point for treatment for the waiting list group. For participants in the EMDR group, additional treatment-related assessments take place within sessions (see later).

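### T1 is given as both 2 months and 10 weeks, and the only explicit origin for T2, the start of treatment, is undefined for the waiting list, so the text states no common clock for the two arms

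*Protocol article*

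**What the plan says.** Four places in the protocol article bear on when the outcomes are measured.

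- **Recruitment** (closing sentences): the measures are taken at baseline, "again following treatment at 2 months (T1), and then 6 months (26 weeks) after treatment started (T2". No separate rule is given for the control arm.
- **Abstract, Methods**: a blinded assessor "will assess outcomes at baseline, 10 weeks, and 6 months".
- **Outcome measures**: the instruments are "administered at baseline (T0), post treatment (T1, at 10 weeks), and at 6-month follow-up (T2".
- **Note under Fig. 2**: "T2 is the starting point for treatment for the waiting list group".

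Three further statements matter. Under Randomization, allocation concealment, and blinding: "After T0, participants will be randomly assigned to either the EMDR or treatment as usual group". No maximum interval from randomisation to the first session is stated. The abstract describes the therapy as "nine sessions, around 60 min in length delivered weekly". Quantitative data analysis enters time as a categorical variable and estimates effects at post treatment and at six months, so both visits carry a between-arm comparison. No single primary time point is named.

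**The concern.** There are two defects of different weight.

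The lighter one is that T1 has two values. Two months and ten weeks are not the same visit date, and site staff could book from either section.

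The heavier one is the time origin. The article expressly counts a visit from something only once, and that something is the start of treatment. In the EMDR arm this event comes some time after randomisation. In the waiting-list arm it does not happen until T2. The label for T1, a visit after treatment, likewise marks no event in the control arm. Someone booking control visits has to supply an origin that the text does not give.

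At stake is whether the arms are compared at equal times since randomisation. If EMDR visits follow the therapy calendar and control visits are booked from baseline, EMDR participants are measured later. A model with categorical time gives both visits the same label and cannot see the difference. If symptoms drift downward over time in both arms, later EMDR visits would favour EMDR.

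**Working it through.** **Inputs.** T1 at 2 months, and T2 at 6 months (26 weeks) from treatment start (Recruitment). T1 at 10 weeks (abstract, Outcome measures). Control treatment start at T2 (note under Fig. 2). Nine weekly sessions (abstract). Randomisation after T0 (Randomization section). The delay *d* from randomisation to session 1 is not given. I assume a range of 0 to 8 weeks.

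**Step 1, the plan's own conversion.** One month = 365.25 / 12 / 7 = 4.35 weeks. Six months = 6 × 4.348 = 26.1 weeks, which agrees with the stated 26.

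**Step 2, T1.** Two months = 2 × 4.348 = 8.7 weeks. Ten weeks = 10 / 4.348 = 2.3 months. The two statements differ by 10 − 8.7 = 1.3 weeks.

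**Step 3, the T2 rule in the control arm.** The rule is T2 = treatment start + 26 weeks. For the waiting list, treatment start = T2. Substituting gives T2 = T2 + 26 weeks, which has no solution.

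**Step 4, the T2 rule in the EMDR arm.** Measured from randomisation, T2 = *d* + 26 weeks:

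| Assumed delay *d* (weeks) | EMDR T2, weeks from randomisation |
|---|---|
| 0 | 26 |
| 1 | 27 |
| 2 | 28 |
| 4 | 30 |
| 8 | 34 |

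A control visit booked at 26 weeks from randomisation would match only the first row.

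**Step 5, T1 and the last session.** From session 1 to session 9 is 8 weeks.

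- If T1 is counted from treatment start, both 8.7 and 10 weeks fall after session 9.
- If T1 is counted from randomisation, session 9 falls at *d* + 8 weeks. It precedes a two-month T1 only if *d* is below about 8.7 − 8 = 0.7 weeks. It is no later than a ten-week T1 only if *d* is at most 10 − 8 = 2 weeks.

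None of this changes a sample-size figure.

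**The case against.** The strongest reply is that a shared schedule is plainly intended. The abstract lists baseline, 10 weeks and 6 months for all participants. Outcome measures does the same without separating the arms. The eligibility criteria speak of a six-month trial duration for everyone. The article also calls T0 a pre-treatment measurement in both arms, so treatment-based wording may be a phase label rather than a literal origin. Figs. 1 and 2 could not be seen and may show a time axis. The article condenses a fuller protocol version, where visit windows would normally be found.

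Much of this stands. It rules out saying that the arms *are* on different calendars. A reader might infer that from the Recruitment sentence, but nothing in the article says that control visits follow another timetable. It does not remove the defect, however. The suggested baseline origin is never written out, and the one origin that is written out conflicts with it and cannot be applied to controls.

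A reader might also try to size the bias from the planning trial: 69.9 − 56.5 = 13.4 CAPS points, or 1.34 points per week if spread evenly over ten weeks. That would give about 1.34 × 1.3 = 1.7 points for the T1 mismatch and 1.34 × 4 = 5.4 points for a four-week delay for make-up sessions. The documents support neither figure:

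- The two T1 values describe one visit that applies to both arms. If everyone is seen at 8.7 weeks, or everyone at 10, the asymmetry is zero.
- No section provides for make-up sessions or postpones T1 for them.
- The slope subtracts a waiting-list mean from an overall baseline and assumes steady change over a period that the article does not give.

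Nor does the article show that T1 precedes session nine. As step 5 shows, that requires counting from randomisation together with a late start. It is also conjecture that assessors would guess the arm from visit timing. The blinding section keeps assessors away from therapists and has another assessor repeat the measurement after any unblinding.

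**Conclusion.** The point holds as a contradiction and an unworkable definition. T1 has two values 1.3 weeks apart. The only explicit origin for T2 does not exist in the waiting-list arm before T2 itself. The text therefore states no common time origin for the T1 and T2 comparisons of the primary outcomes, although two sections suggest one.

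The T2 origin is the weightier part. Followed as written, it shifts EMDR T2 by the full delay to session 1, to 26 to 34 weeks after randomisation under the assumed 0 to 8 weeks. The analysis would still treat that visit as the same time point as the control visit. Neither the actual delay nor the rate of change per week is in the document, so no bias in CAPS points can be stated. The conclusion is also conditional on the unseen figures: a clear time axis in Fig. 1 or Fig. 2 would show the intent, but the Recruitment wording would still need correcting.

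This should be amended. It goes beyond a clerical slip because it governs how visits are booked, which an analysis plan cannot repair afterwards.

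**What to change.** Reconcile the abstract, Recruitment, Outcome measures and the note under Fig. 2 to one schedule:

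- T1 at one stated week. Ten weeks already appears in two of the places.
- T2 at 26 weeks.
- Both counted from randomisation, in both arms, with the same visit window and regardless of how far therapy has progressed.
- The therapy-based phrases that define T1 and T2 in the Recruitment sentence replaced by these week numbers.

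The cost is protocol wording and assessment scheduling. Treatment and sample size are unaffected. The drawback is that some EMDR participants with a late start or delayed sessions will be assessed at T1 before their last session. With weekly sessions and T1 at 10 weeks, that happens once the start is more than 2 weeks after randomisation. This is the price of comparing the arms at equal times since randomisation.

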### Randomization, allocation concealment, and blinding

Consenting participants will receive the pre-treatment (T0) measurements. After T0, participants will be randomly assigned to either the EMDR or treatment as usual group. An independent research manager at the District Health Board research office (who is not involved in the study) will generate the random sequence. This allocation sequence will be computer-generated and non-stratified with varying block sizes, which will not be disclosed to the researchers to ensure concealment. After randomization, the research office will notify the trial coordinator from the research team as to the allocation. To ensure allocation concealment, the randomization code will not be released until after the participant has been recruited into the trial, which takes place after all baseline measurements have been completed.

After allocation, the participants will be informed which group they are in. Hence, neither the participants nor the specialized therapists who deliver EMDR will be blinded to the allocation (as it is not practical to undertake blinded EMDR). However, outcome assessors will be blinded to treatment allocation, as will those performing data entry and the trial statistician (MW). Assessors and therapists will emphasize the importance of blinding to the participants and remind them not to reveal the randomized treatment condition. Assessors will avoid contact with the therapists and other caregivers. Assessors will be asked to report any case of unblinding, in which case, another assessor will repeat the entire measurement.

### Therapist training requirements

The treatment sessions will be delivered by consultant psychiatrists and clinical psychologists who have completed at least basic training in in an EMDR International Association (EMDRIA)-recognized program and have experience working with people with SMI. The exact criteria are as follows.

All EMDR therapists must:
Be practicing mental health clinicians with full registration to practice as clinical psychologists or psychiatrists, with a current practicing certificate issued by the New Zealand Psychologists Board (for psychologists) or by the New Zealand Medical Council (for psychiatrists)Have at least 5 years of experience working with people with serious mental illnessHave completed both EMDR Basic Training Stage 1 and Stage 2 (as a minimum) in a training program recognized by the EMDRIA

Therapists will be supervised by a senior professional certified in EMDR.

Ten percent of sessions will be observed and reviewed for treatment fidelity using the EMDR Fidelity Rating Scale [33], which evaluates adherence to EMDR’s eight-phase/three-pronged protocol.

### Intervention

#### Choice of comparators

While the importance of trauma is increasingly being recognized [1–10], New Zealand forensic mental health services do not systematically screen for PTSD or routinely offer trauma-focused psychological therapy (such as EMDR or trauma-focused cognitive behavioral therapy (CBT)). There is no trial-based evidence investigating whether EMDR in this group is effective. This trial is a superiority trial which investigates whether treatment with EMDR improves outcomes in reducing PTSD symptomatology (alongside other important outcomes described in the following) when added to treatment as usual, compared to treatment as usual alone.

#### Treatment as usual

Participants in both groups—EMDR and waiting list—receive treatment as usual, consisting of antipsychotic medication and multidisciplinary treatment by psychiatrists, psychologists, social workers, occupational therapists, key workers, and cultural workers. Psychotic illness will be treated by a multidisciplinary approach in accordance with the Royal Australian and New Zealand College of Psychiatrists clinical practice guidelines for the management of schizophrenia and related disorders [34]. Treatment as usual will be considered equal in both conditions as a result of the randomization procedure and participants receiving similar care within the same service.

#### Experimental intervention: EMDR

In addition to treatment as usual, the participants randomized to EMDR will undergo nine sessions of EMDR therapy, each 60-min long. The first session will involve assessment and planning, and the subsequent eight sessions will involve active EMDR treatment.

In the first session, the treatment rationale will be explained. The therapist will receive information from the Interview for Traumatic Events in Childhood (ITEC), a reliable and valid tool for assessing early traumas [35]. The ITEC captures categories (e.g., sexual abuse, physical abuse) of experienced traumatic events. In addition, the intensity of re-experiencing symptoms of each traumatic event is assessed. Based on the ITEC, the therapist draws up a preliminary, formatted EMDR case conceptualization (when crucial memories are identified for reprocessing [36]), which they discuss and complete together with the patient in the first session. This results in a hierarchy of the most relevant traumatic memories in order of significance with regard to the symptoms of PTSD.

During the next eight sessions, the identified traumatic memories will be processed following the basic EMDR protocol. The participant is asked to focus on the currently most distressing image of a memory in a multimodal manner, including its image, thought (an experienced negative cognition (NC) and a healthier positive cognition (PC)), emotion, physical sensation, and level of tension. The patient then rates this memory on a subjective unit of distress (SUD) scale from 0 to 100. Processing of the memory starts when the therapist asks the patient to hold the target image in mind while concentrating on a distracting stimulus (the finger of the therapist eliciting eye movements) for about 30 s. The patient reports briefly what comes to mind and is guided by the clinician to refocus on that element while focusing on the distracting stimulus. This continues until no more associations come up and the disturbance level associated with the target memory (SUD) drops to zero.

The therapist then guides the participant in installing the PC to a maximum validity, that is, a Validity of Cognition (VOC) scale score of 7 (a “completely true” rating). The participant identifies any residual disturbing sensations and, if present, the physical disturbance is processed in the same manner as already described. The therapist facilitates a positive closure to the session. In the next session, a re-evaluation takes place in which the participant comments on previously processed targets as a basis for further intervention.

